## Discussion

Patellar tendinopathy mainly occurs in young adults who practise sports, either professionally or as amateurs, which involve repeated running, hopping and jumping [52], with typical clinical and imaging diagnostics features [53].

To minimise uncontrolled factors that could affect the results, this study only includes male patients, as the viscoelastic properties of skeletal muscle and tendon are driven by hormone expression [54]. Disorders of insulin and thyroid hormones metabolism are related to tendinopathy both in vitro and in vivo [55], and sex hormones may promote changes in the structure of tendons, thus influencing their response to physical exercise [56]. If we obtain positive results in this study, a new study will be performed on female subjects only.

Both the cellular and applied LP-PRP treatments are based on safety and efficacy criteria obtained in animal studies and in clinical trials in which these treatments were applied successfully to treat other musculoskeletal pathologies [17, 18, 22, 29, 31–33, 41]. Future studies should try to establish the optimal cellular dose or the appropriateness of multiple doses. The composition and volume of the cell suspension medium should also be noted, as these variables can influence results.

Applying the guidelines of the Helsinki declaration of the World Medical Association, we have avoided using a true placebo in the control group, and plan to use an active control LP-PRP group. We hypothesise that this control treatment is very unlikely to exert the significant regenerative effect that we would attribute to MSC. However, this hypothesis must be confirmed, as no previous clinical trials have analysed the therapeutic effect of expanded BM-MSCs in patellar tendinopathy. The present study has several trengths. This is the first study to assess the effect of injecting autologous mesenchymal cells into the pathological zone of refractory proximal patellar tendinopathy in athletes. The study will monitor clinical scores, strength and imaging findings including 2D US, UTE MRI and ultrasound tissue characterization (UTC). The addition of UTE MRI and UTC will enable more precise measurement of structural tendon changes than 2D US. The control group will be offered mesenchymal cell therapy if the results of the control group prove ineffective. We are fully aware of the limitations of the present study. For example, the control group will receive active LP-PRP treatment rather than a true placebo, limiting the value of a control group. However, it will be easier to recruit athletes in a study with a control treatment that is perceived to be effective in an athletic cohort. The sample size is small, limiting the power of this study. Finally, this study fails to establish an optimal cell dose, which should be examined in future studies.

It is important to plan a second open experimental phase, where patients treated with LP-PRP who have not improved will be offered cell treatment. This approach, in addition to providing subjects included in the control group with a potentially more effective treatment, should also help determine the scope of the therapeutic effect of the MSC on LP-PRP, establishing a comparative cost-effective index.

This clinical trial also aims to advance current knowledge about the pathology of interest, and the hypothetical regenerative effect of incorporating innovative diagnostic systems and evaluations of this type of lesions. Both UTE magnetic resonance (Ultrashort Echo TE) and UTC are innovative non-invasive techniques that allow us to quantify regenerative effects using imaging.

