#### LP-PRP control group

Ten patients will be treated with two doses of LP-PRP, each containing 6 mL of solution-PRP. The second dose will be injected 23 days after the first one.

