### Experimental phase B

Results will be evaluated 6 months after the treatment. If the results support the hypothesis that a higher efficacy is obtained in the MSC group, the cell therapy trial will be offered to subjects from the LP-PRP group who show no evidence of clinically relevant improvement: if they wish, this group will be treated with MSC. This will be ‘experimental phase B’, which will be evaluated with the same clinical and imaging assessment protocol as described above.

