### Response evaluation

Subsequent assessments following the treatment include AE review, VAS (pain), VISA-P Questionnaire, ultrasound imaging (conventional ultrasound, UTC and MRI), dynamometry manual test and clinical assessment (Table 2 for phase A, and Table 3 for phase B). These will take place at 1, 2, 3, 6, 8 and 10 weeks and 3, 6, 12 months post-treatment.

**Table 2 Tab2:** Outcome assessments experimental phase A

Study period															
	Enrollment				Treatment		Follow-up								
Timepoints					0	23 days	1 week	2 weeks	3 weeks	6 weeks	8 weeks	10 weeks	3 months	6 months	12 months
Inf. sheet	X														
Incl/excl Criteria		X													
IC		X													
Preop + serology			X												
Allocation				X											
ClinicalHistory	X	X													
Physical exam	X	X					X	X	X	X	X	X	X	X	X
VAS		X					X	X	X	X	X	X	X	X	X
VISA-P		X					X	X	X	X	X	X	X	X	X
blood test													X		
Group MSV BM					X										
Group MSV saline sol.					X										
Group MSV MSV						X									
Group PRP BM sham					X										
Group PRP PRP					X	X									
Bloodbank					X										
MRI		X											X*		X
Ultrasound		X					X	X	X	X	X	X	X	X	X
UTC			X						X		X		X	X	X
DYN			X						X		X		X	X	X
AE					X	X	X	X	X	X	X	X	X	X	X
Medication					X	X	X	X	X	X	X	X	X	X	X

*Elig.* eligibility, *IC* informed consent; *VAS* visual analogue scale; *VISA-P* Victorian Institute of Sport Assessment (Patellar); *BM* bone marrow harvest; MSC Infusion of MSC; *MRI* magnetic Rresonance; *UTC* ultrasound tissue characterisation; *DYN* dynamometry, *PreOp* preoperative study, *AE* Adverse Events.

*X** if the *VAS* and *VISA-P* scales show a significant improvement, and *MRI*, *US*, and UTC provide evidence of healing, the result will be considered positive and the patient will be followed up with confirmation controls at 6 and 12 months. For safety reasons, according to AEMPS criteria, a control test will be performed after the trial, within a period of 2 years after treatment.

If the 6-month evaluation shows negative results, patients may be transferred to the open experimental phase B.

**Table 3 Tab3:** Outcome assessments experimental phase B

Study period															
	Enrollment			Treatment		Follow-up									
Timepoints				0	23 days	1 weeks	2 weeks	3 weeks	6 weeks	8 weeks	10 weeks	3 months	18 weeks	6 months	12 months
IC		X													
Preop + serology			X												
Physicalexam	X	X				X	X	X	X	X	X	X	X	X	X
VAS		X				X	X	X	X	X	X	X	X	X	X
VISA-P		X				X	X	X	X	X	X	X	X	X	X

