### Pain and function

Pain will be recorded on the VAS, and function will be evaluated by measuring extension forces in the knee using a manual dynamometer.

The pain and functional evaluation will be performed using the VISA-P score, which specifically evaluates pain and function in patellar tendinopathy. The scale ranges from 0 to 100, where a value of 100 indicates the absence of pain at rest, when walking, when climbing up or downstairs or during exercise [50]. VISA-P score values for patients with chronic patellar tendinopathy usually range from 30 to 50. Physical activity may be undertaken again if values are above 60. Patients with score values over 70 are considered fit for competition, although demands are higher for professional athletes. The minimum significant difference has been set at 13 points.

The following VISA-P criteria are used to assess improvement in this trial [51]:
Desired: ≥ 60/100 (after 3 months)Very satisfactory: ≥ 70/100 (after 6 months)Ideal: ≥ 80/100 (after 12 months)

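### Phase B is credited with informing the effect of MSC relative to LP-PRP and a cost-effectiveness index, but an open, single-arm extension in LP-PRP non-improvers can only describe change after MSC

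*Protocol article*

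**What the plan says.** The Discussion introduces phase B with this sentence: "It is important to plan a second open experimental phase, where patients treated with LP-PRP who have not improved will be offered cell treatment". It names access to a potentially more effective treatment as one benefit, then adds that the phase "should also help determine the scope of the therapeutic effect of the MSC on LP-PRP, establishing a comparative cost-effective index".

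The design of phase B is set out elsewhere in the article:

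- **Population.** Under Experimental phase B, cell therapy is "offered to subjects from the LP-PRP group who show no evidence of clinically relevant improvement", and "if they wish, this group will be treated with MSC".
- **Condition.** The same section makes the offer depend on the 6-month results supporting higher efficacy in the MSC group. Background says much the same. The abstract and the note to Table 2 omit this condition, which does not affect the present point.
- **Blinding.** The note to Table 2 says that after a negative 6-month evaluation "patients may be transferred to the open experimental phase B".
- **Size and earlier treatment.** Entrants come from the LP-PRP control group, of which the article says: "Ten patients will be treated with two doses of LP-PRP".
- **Measurements.** Table 3 repeats the clinical and imaging set of phase A, with a pre-treatment assessment in its enrolment columns.

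On the size of a relevant VISA-P change, Pain and function says: "The minimum significant difference has been set at 13 points".

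**The concern.** The sentence gives phase B data a comparative meaning that the design does not provide. Estimating the effect of MSC relative to LP-PRP needs comparable patients treated each way over the same period. In phase B everyone receives MSC, knows it, and was selected because the earlier result was poor. A comparative cost-effectiveness index needs that same effect estimate, so it fails for the same reason, whatever costs are recorded.

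If the sentence is followed, improvement after the switch could be reported as MSC succeeding where LP-PRP failed, and then carried into a value-for-money figure. Some improvement is expected even if MSC does nothing. The limitations listed in the Discussion cover the active control, the sample size and the cell dose, and do not mention phase B.

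**Working it through.** The article gives no figure for phase B to reproduce. The check has two parts.

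**1. Claim against design**

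| Needed for a comparative effect | What the article gives phase B |
|---|---|
| Concurrent control | None; every entrant receives MSC |
| Comparable groups | Selected LP-PRP non-improvers who choose to enter |
| Masked treatment | Open |
| The question MSC versus LP-PRP | MSC after two LP-PRP doses, the rehabilitation programme and at least 6 months |
| A result independent of phase A | Opened only if phase A already favours MSC |

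Cost-effectiveness is absent from the objectives, from Tables 2 and 3 and from Statistical analysis.

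**2. Size of the problem (illustration)**

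From the article: at most 10 entrants, and a 13-point minimum VISA-P difference. Assumed, because the article gives no such values: VISA-P SD 15 to 20, correlation ρ between repeated measurements 0.5 to 0.9, and mean LP-PRP gain *m* at 6 months of 10 to 20 points. A 6-month gain below 13 points stands in for the entry rule.

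*Regression to the mean.* Let each score be a stable patient level plus independent error of variance (1 − ρ)SD². The 6-month gain D then has SD s = SD·√(2(1 − ρ)). The later change (follow-up minus 6-month score) has covariance −(1 − ρ)SD² with D, so the regression slope is −1/2. With no MSC effect:

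expected rise given D < 13 = ½ · s · φ(z)/Φ(z), where z = (13 − m)/s.

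- Lowest case (SD 15, ρ 0.9, m 10): s = 6.71, z = 0.447, φ/Φ = 0.537. Rise = ½ × 6.71 × 0.537 = 1.8 points, and 1.8/13 = 14%.
- Middle case (SD 15, ρ 0.7, m 20): s = 11.62, z = −0.602, φ/Φ = 1.217. Rise = ½ × 11.62 × 1.217 = 7.1 points, and 7.1/13 = 54%.
- Highest case (SD 20, ρ 0.5, m 20): s = 20, z = −0.35, φ/Φ = 1.033. Rise = ½ × 20 × 1.033 = 10.3 points, and 10.3/13 = 79%.

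Simulation of the same model agrees. It also shows that 4% to 44% of entrants would gain a further 13 points or more with no MSC effect.

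Two conditions matter. These figures apply when change is counted from the 6-month value used for selection. If change is counted from a fresh pre-MSC measurement with independent error, this component vanishes in the model; where errors persist over time, some of it remains. The entry rule matters too: selecting on a 6-month VISA-P below 60, with an assumed baseline mean of 40, gives 0.6 to 8.0 points.

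*Precision.* The 95% half-width for a mean change is t × SD of change/√n, with an assumed SD of change of 10 to 20.

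- n = 10: 2.262 × 10/√10 = 7.2, up to 14.3.
- n = 5: 2.776 × 10/√5 = 12.4, up to 24.8.

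Even a purely descriptive mean change is therefore uncertain by about as much as the minimum difference.

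**The case against.** The best defence is that the sentence is a loosely worded aspiration. It says the phase should also help, Background gives feasibility as a reason for the offer, and the Discussion names access to treatment as well. No objective or planned analysis depends on a phase B comparison. The main objective compares the randomised groups, and phase B opens only after that comparison. This stands, and it limits the point to one claim and its wording. It does not rescue the claim: the index is stated without its own hedge, and no careful analysis of phase B would yield the comparison.

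A reader might infer more than the article supports:

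- *That the comparison is the sole purpose of phase B.* The article gives the other reasons just named.
- *That the trial collects no cost data.* The article lists none, but it condenses a full protocol that is not shown, and unit costs need not appear in a visit schedule.
- *That phase B will be pooled with, or tested against, phase A.* Nothing says so.
- *That phase B lacks its own baseline.* Table 3 schedules one.
- *That entrants repeat the marrow harvest.* In phase A the LP-PRP group had a sham harvest only.
- *That regression to the mean would by itself reach the relevant difference.* Every mean computed above stays below 13 points.

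The selection rule used in the working is also a simplification. Criteria for non-response to treatment judges clinical change from physical examination, VAS, VISA-P and dynamometry together.

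**Conclusion.** The point holds in limited form. The Discussion credits phase B with comparative and cost-effectiveness information that its design cannot produce. Phase B can describe change after MSC in at most 10 selected LP-PRP non-responders, and no more. This conclusion follows from the design and needs no assumed figure.

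The illustration shows that the distortion need not be trivial: about 2 to 10 VISA-P points from regression to the mean, or 14% to 79% of the 13-point minimum difference, before expectation or natural course. That range rests on the assumed SDs, correlations, LP-PRP gains and entry rule, and on counting change from the 6-month value. A fresh baseline would reduce it, but would not remove expectation or natural course or create a comparator.

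No endpoint, sample size, allocation or planned phase A analysis is affected. The wording should be changed, because following it as written would lead to an unsound conclusion and correcting it costs little.

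**What to change.** - In the Discussion, delete the statement that phase B helps determine the effect of MSC relative to LP-PRP and establishes a comparative cost-effectiveness index.
- Under Experimental phase B, state that the phase is descriptive: it reports change from the pre-MSC baseline already scheduled in Table 3, in LP-PRP non-responders, without attributing that change to MSC over LP-PRP.
- State in the same place that conclusions on MSC versus LP-PRP rest on the randomised phase A comparison, before any switch at 6 months.

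The offer of cell treatment, the visits and the measurements stay as they are. The cost is a few sentences and the loss of a claim that the design cannot support. The comparison then rests on 10 patients per arm, whose limited power the article already admits.

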## Trial Status

Protocol version: V2. 05-July 2017Recruitment starts December 2017.Total subjects recruited on 28-10-2018: 20

## Data Availability

Not applicable.

## Abbreviations

AE (AA): Adverse event
AEMPS: *Agencia Española de Medicamentos y Productos Sanitarios* (Spanish Agency for Medicines and Healthcare Products)
CEIM: Ethics Committee for ClinicalResearch with Drugs
CRO: Clinical Research Organization
DYN: Dynamometry
FAS: Full analysis set
FFE: FAST FE Sequence (Ultrafast Gradient Echo Sequence)
GMP: Good Manufacturing Practices
IBGM: *Instituto de Biología Genética Molecular* (Institutefor Molecular Biology and Genetics)
ITRT: *Institut de TerapiaRegenerativaTissular* (Institute for Tissue Regeneration Therapy)
LP-PRP: Leukocyte-poor platelet-rich plasma
MO: Bone marrow
MRI: Magnetic resonance imaging
MSC: Mesenchymal stem cells
MSV: Mesenchymal stem cells from valladolid
PEI (IMP): Investigational medicine product
PP: Per protocol analysis
PRP: Platelet-rich plasma
ROI: Region of interest
SAE (AAG): Serious adverse event
T2: T2 sequence
UTC: Ultrasound tissue characterisation
UTE: Ultrashort echo time sequence
VAS: Visual analogue scale for pain
VISA: ‘Victorian Institute of Sport Assessment’ scale
VISA-P: ‘Victorian Institute of Sport Assessment (patellar)’ scale
